## Abstract

**Introduction:**

Although Chronic Obstructive Pulmonary Disease (COPD) is generally considered a progressive condition with limited reversibility, recent data suggests potential for lung function improvement with exercise. Mechanistic insights into exercise-induced benefits remain limited, but in vitro models offer promise for understanding cellular and molecular changes. This study aims to elucidate the mechanisms behind lung tissue regeneration in COPD through adapted exercise training as well as validating advanced lung function tests, such as Impulse Oscillometry (IOS) and Airspace Dimension Assessment (AiDA) for improved detection of early physiological /structural changes and predicting clinical outcomes.

**Methods:**

This is the protocol of a multicenter, hypothesis-generating, single-arm study exploring the mechanisms for lung regeneration in subjects with COPD induced by exercise. The exercise protocol includes supervised and individually tailored moderate-intensity aerobic- and muscle strengthening exercise, performed three times per week for 12 weeks. Eighty sedentary adults with a clinically stable COPD will be recruited at two study sites. Included participants will be assessed at baseline and at 12 weeks by comprehensive pulmonary function testing (including spirometry, IOS, body plethysmography, diffusing capacity of the lung, single breath nitrogen wash-out, AiDA, questionnaires, physical capacity performance (including 6-minutes walking test (6MWT), one-minute sit-to-stand test, and cardiopulmonary exercise testing (CPET)), and collection of blood and urine samples and bronchoscopy. A mid-intervention assessment at week 6 will include medication use, health status, questionnaires, spirometry, and blood sampling.

**Discussion:**

Understanding the molecular and cellular activities related to lung function induced by exercise provides insights into repair pathways, challenges the notion of irreversible lung damage in COPD, and paves the way for improved management strategies with potential identification of biomarkers and pharmacological interventions.

**Trial registration:**

ClinicalTrials.gov ID NCT06335992 (Registration date 2024-03-28).

**Supplementary Information:**

The online version contains supplementary material available at 10.1186/s12931-025-03443-y.

## Background

Chronic obstructive pulmonary disease (COPD) is an increasing global health burden characterized by persistent airflow limitation and progressive destruction of lung tissue with no cure, leading to significant patient suffering and placing a considerable strain on healthcare systems [1]. The pathogenesis of COPD is primarily driven by long-term exposure to noxious agents—most notably tobacco smoke, but also air pollution, occupational hazards, genetic predispositions (e.g., alpha-1 antitrypsin deficiency), and early-life factors such as prematurity and recurrent respiratory infections. These exposures contribute to chronic epithelial injury, persistent inflammation, and remodeling of the extracellular matrix (ECM), ultimately leading to airflow limitation and clinical phenotypes such as chronic bronchitis and emphysema [2].

A hallmark of COPD is physical inactivity and poor physical capacity, both of which are associated with increased mortality, higher hospitalization rates, reduced health-related quality of life, and limited ability to perform daily activities. Pulmonary rehabilitation and structured exercise programs, such as aerobic and resistance training, have consistently been shown to improve functional performance and prolong survival [3–5]. As such, promoting physical activity and supporting patient self-management are key components of long-term COPD care. However, despite well-established clinical benefits, the underlying cellular and molecular responses to exercise in COPD remain poorly understood. Moreover, current pharmacological treatments primarily alleviate symptoms and reduce exacerbation frequency but do not halt or reverse the underlying pathophysiology. Gaining mechanistic insight into the biological responses to exercise is therefore essential for the development of disease-modifying and personalized therapeutic strategies.

COPD is a heterogeneous disease with substantial interindividual variability in underlying pathology. Central mechanisms include oxidative stress, chronic inflammation, and increased proteolytic activity. The inflammatory response may be dominated by neutrophils, eosinophils, or macrophages, often accompanied by elevated cytokines such as TNF-α, IL-1β, and IL-6. Structural changes including small airway remodeling, mucus hypersecretion, and alveolar destruction, vary in extent and contribute differently to clinical manifestations. A key driver of ECM degradation is the imbalance between matrix metalloproteinases (MMPs) and their endogenous inhibitors (TIMPs), resulting in excessive proteolysis of critical ECM components like elastin and collagen. This impairs alveolar integrity, reduces lung compliance, and contributes to air trapping and hyperinflation, hallmarks of progressive lung function decline [6, 7].

The general understanding has until now been that once COPD is established, it is irreversible and linked to a gradual loss of lung function over time. However, recent data from observational studies on COPD cohorts indicate that not all subjects decline in lung function, some even show improvements over time [8, 9]. The ability of adult human lung growth and alveolarization after pneumonectomy has been demonstrated in a case report study, where exercise and induced stretch were relevant contributions to the success [10]. Altogether, this indicates that the human lung has an inherent capacity to self-renewal.

This project therefore aims to uncover the mechanisms of exercise-induced lung regeneration, with a focus on improving disease monitoring and individualizing therapy.

To obtain deeper mechanistic insights into the in vivo molecular and cellular activities induced by physical exercise, we aim to do an extensive evaluation of subjects with a stable COPD before and after a 12-week intervention program. The exercise intervention is specifically tailored to stimulate the distal regions of the lung, areas most severely affected in COPD and essential for efficient gas exchange. Traditional lung function tests, such as spirometry, are often insufficient for detecting subtle changes in these peripheral lung compartments. Therefore, we aim to validate advanced, non-invasive techniques, including Impulse Oscillometry (IOS) [11] and Airspace Dimension Assessment (AiDA) [12], which offer improved sensitivity for assessing small airway and distal lung involvement. These methods may enhance the early detection of physiological changes and improve the prediction of clinical outcomes.

To complement the in vivo data, we will replicate exercise-related conditions in an in vitro bioreactor system developed in house, designed to mimic the lung’s microenvironment and mechanical forces [13]. This platform integrates cyclic stretch, mimicking in vivo breathing, with 3D cell culture systems using decellularized lung slices (DLS) and precision-cut lung slices (PCLS), enabling the study of tissue regeneration and extracellular matrix dynamics in both healthy and COPD-affected lung tissue. The findings will have implications for both basic science and clinical practice, by informing the design of more effective, targeted exercise protocols and enabling the monitoring of biological responses through accessible biomarkers in blood samples. By integrating physiological measurements with biomarker profiling and imaging, we aim to refine disease phenotyping, optimize diagnostics, and ultimately personalize COPD management. Ultimately the in vitro studies are aimed to find new targets for treatment of COPD that can act synergistically with physical exercise.

We hypothesize that individually adjusted physical exercise leads to; (1) reduction in harmful remodeling processes linked to oxidative stress, inflammation, and remodeling, and (2) activation of beneficial regenerative pathways. We also aim to identify and validate biomarkers that reflect these biological responses, both as indicators of lung regeneration and as potential therapeutic targets.

## Methods/Design

### Main objective

The main objective of this project is to identify mechanisms for lung regeneration in subjects with COPD induced by physical exercise. Our hypothesis is that adjusted physical exercise improves disease outcomes in these subjects by [1] decreasing remodeling processes linked to oxidative stress, and inflammatory and/or immunological pathways in the lung [2], inducing remodeling processes linked to healthy regeneration of lung tissue. Along the way, we also expect to identify (or validate) biomarkers mirroring systemic processes such as reduced inflammation and ongoing remodeling. These events may additionally act as potential targets for interventions.

### Specific aims

Study the effects of physical exercise on lung function parameters linked to structural properties e.g., elasticity, stiffness and distal air space dimensions.Validate IOS and AiDA as sensitive and non-invasive tools for detecting changes in lung physiology, and determine their correlation with CT-derived emphysema measures.Evaluate the effect of physical exercise intervention on lung physiology as measured by IOS and AiDA, and assess how these changes relate to changes in symptom burden and quality of life.Evaluate changes in biomarkers before and after the exercise intervention related to regenerative processes, extracellular matrix turnover, stem/progenitor cell activity, and inflammatory patterns in lung tissue biopsies, blood- and urine samples. Correlate these changes with: (a) pulmonary function testing indices, (b) physical capacity, (c) health-related quality of life.Explore the association between structural lung changes, as characterized by high-resolution computed tomography imaging (HRCT), and systemic biological responses, as measured by circulating and urinary biomarkers.Investigate cellular behavior and tissue remodeling/regenerative responses in vitro using models derived from COPD subjects and evaluate how these processes are modulated by exercise-induced systemic changes.

### Trial design

This trial, “Tissue Regeneration and Exercise” (T-REX), is designed as a multi-center exploratory, hypothesis-generating single group trial exploring the mechanisms for lung regeneration in people with COPD induced by a 12-week exercise intervention. The project is divided into four parts; [1] basic baseline survey and testing; [2] a 12-week exercise intervention; [3] analysis phase; and [4] in vitro characterization. Figure 1 gives an overview of the study design.

**Fig. 1 Fig1:**
[figure not shown]
Overview of study design

This protocol is developed in compliance with the SPIRIT 2013 guidelines for reporting clinical trial protocols [14]. Figure 3 provides an overview of the SPIRIT schedule for enrolment, intervention, and assessment, and a SPIRIT checklist is included as Additional file 1. The intervention details are structured following the guidelines of the Template for Intervention Description and Replication (TIDieR) [15] (Additional file 2) and the Consensus on Exercise Reporting Template (CERT) [16] (Additional file 3).

### Study setting/participating centers

The study will be conducted at two study sites in Sweden: Lund and Uppsala. Principal investigators in Lund are [name] and [name] and in Uppsala [name] and [name]. The following centers will be involved in the project.

Lund University, Lund, Sweden.Region Skane, Lund, Sweden.Uppsala University, Uppsala, Sweden.Region Uppsala, Uppsala, Sweden.

Enrolment began in 2022 at both sites and is scheduled to run until the recruitment of eligible COPD subjects has been finalized. The first round of recruitment is expected to be completed end of 2025.

### Eligibility criteria

#### Inclusion criteria

Participants will be adults with a diagnosis of COPD. To be eligible for participation in the study, participants must have:

Forced expiratory volume in one second (FEV_1_)/Forced vital capacity (FVC) < 0.7.Postbronchodilator FEV_1_ of 30–85% of predicted value.Optimal medical treatment according to GOLD and the Swedish National Guidelines.Former smokers, ≥ 10 pack-years, smoking history, but had to be an ex-smoker for ≥ 1 year.Free from exacerbations in the last 6 weeks.Age: 50–85 years.BMI: 18–37 kg/m^2^.

#### Exclusion criteria

Individuals may not enter the study if any of the following apply:

Regular participation in exercise sessions (≥ 2 times/week).More than one exacerbation during the 12 months prior to study entry.Long-term oxygen treatment (LTOT).Oral corticosteroids or biological treatment.Desaturation to ≤ 87% at the screening six-minute walk test (6MWT).Alcohol or drug abuse.Unstable cardiovascular or pulmonary disease.Any physical or mental condition, including comorbidities that, at the discretion of the investigator, are considered likely to interfere with safe participation in the exercise program or influence the study outcomes.

### Intervention

#### Intervention description

The 12-week exercise intervention will consist of moderate intensity aerobic and strength training twice per week as “supervised training on site” and once per week as “training at home”. All exercise sessions on site will be conducted in groups of 3–8 people in a public fitness setting and supervised by a knowledgeable and experienced physiotherapist. Supervision of exercise will include providing motivation and feedback and/or modifying exercises as appropriate/required by, for example, changing the resistance, pace or number of repetitions. The physiotherapists will adhere to a single training protocol to ensure standardized delivery of the training across centers, and regular meetings during the trial will be used to check that the procedures are carried out in the same way at both sites.

The supervised training sessions on site will include.

Aerobic exercise for 33 min on a cycle ergometer at a moderate intensity (≥ 60% Wpeak), individually tailored to achieve a perceived exertion level of 3–6 on the Borg CR-10 scale [1]: After 3 min of warm-up at a low intensity, the exercise will be performed in intervals, 2 min at a moderate intensity, 50–60 revolutions per minute (rpm), 1 min at low intensity, 2 min at a moderate intensity etcetera, in total, 10 intervals at moderate intensity. The exercise intensity will be based on symptom limitation and tailored to the individual needs and limitations of the subject. As one exclusion criterion is oxygen saturation (SpO_2_) ≤ 87% at the screening 6MWT, we do not expect that anyone will desaturate during the training. However, if SpO_2_ decreases < 85% during cycling the training will be stopped and commence when SpO_2_ > 90% [17]. If this happens more than once the patient will be excluded.Strength training for 30 min, involving seven exercises targeting major upper and lower body muscle groups. Each exercise comprises three sets with 8–12 repetitions. For the muscle strengthening exercise equipment such as graded elastic bands and handheld dumbbells will be used. The exercise load will be determined by the participant’s ability to complete 10 repetitions for a given exercise and progression will be achieved by increasing the number of sets, weight or elastic band resistance, as guided by the physiotherapist.

The training at home will include aerobic and strength training for about 60 min. To reduce variability and support adherence in the home training, participants will receive detailed instructions, an exercise diary, and the home-training will be followed-up by the physiotherapist on a regular basis.

The aerobic training at home will include individually adapted aerobic training such as walking continuously or in intervals, cycling or swimming.The strength training will include the same exercises, sets and repetitions as in the “on-site training”, but can be changed according to the choice, need and ability of each subject.

All participants will receive a handbook containing information about the benefits of physical training, practical tips on exercise, an exercise diary for home training where they can plan and track their progress, and contact information with the physiotherapist.

### Criteria for discontinuing or modifying interventions

If participants, due to illness or other absences, are unable to adhere to the training protocol, the training period will be extended. In cases where participants experience illness or absence during the intervention, the training period will be extended to ensure that each participant completes a full six-week training program at the end of the intervention.

Participants have to be in a stable state of their COPD disease as the appearance of increased inflammatory markers may be confounding factors in the analysis of the results.

### Strategies to improve adherence to intervention

To enhance adherence the exercise intervention will be tailored to each individual’s needs and current condition. Continuous support and follow up will take part during the training sessions, and all participants will have access to daily support from the trainers via phone or text messages. Participants will be encouraged to always contact the physiotherapist in case of illness or absence and a plan for continuation will be planned and modified when needed.

### Concomitant and post-trial care

Participants will be allowed to continue their regular medication. However, any changes in medication will not be permitted. If an increase in medication for the lung disease is required, it will be considered an exacerbation, resulting in an extension of the training period. The participants are not allowed to start with any other exercise intervention during the time period of the training intervention. All participants will have a patient insurance. Physician contact will be available during the study.

### Patient and public involvement

Patients and/or the public were not involved in the development of the research question, study design, choice of outcome measures, or recruitment process. This decision was based on the exploratory and mechanistic nature of the study, which primarily focuses on physiological, molecular, and imaging outcomes. However, participants are actively engaged in the intervention phase through their involvement in the tailored exercise program.

### Study outcomes

The primary outcome is to validate the effect in protein profiles after exercise intervention in lung tissue biopsies, blood- and urine samples using proteomic analyses such as multi-plex ELISA, OLINK, and mass spectrometry. Primary factors include; matrix turnover/remodelling proteins: MMPs, TIMPs, MMP-degraded collagen peptides, desmosine, periostin, decorin; growthfactors: VEGF, HGF, PDGF, FGF-2, angiopoietin; inflammatory/immune markers: TNF-a IL-6, IL1-b, IL-8, IL-10, IL-17, MCP-1, CXCL10, CXCl13.

### Secondary outcomes

The secondary outcomes are to validate the effect of training to:

Identify responders and non-responders based on measurements of vital lung parameters (e.g., IOS, FEV_1_, DLCO, AiDA) and physical capacity (6MWT, sit-to-stand test) after exercise intervention.Identify changes in biomarkers related to regenerative processes, matrix turnover, stem/progenitor cell activity, and inflammatory patterns in lung tissue biopsies, blood- and urine samples, and correlate these changes with vital lung parameters (e.g., IOS, FEV_1_, DLCO, AiDA) and measures of physical capacity (e.g., 6MWT, sit-to-stand test).To validate the effect of the exercise intervention on vital lung parameters based on established and novel lung function measurements e.g., IOS, spirometry, DLCO, AiDA, Cardiopulmonary exercise testing.To validate the effect of the exercise intervention on the physical capacity based on established measurements 6-MWT, sit-to-stand test.

### Other secondary outcomes

Other secondary outcomes are to validate:

Improved health-related quality of life parameters after exercise intervention.Improved exercise capacity.Validate if gender and age are confounding factors for the effect of the exercise intervention.

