### Sample size

This is an exploratory study designed to include 80 subjects with clinically stable COPD (assuming a 10–20% drop-out rate) to accommodate various degrees of biological variations in the different exploratory outcome measures. Of these, 20 will also undergo bronchoscopy. Findings that do not reach statistical significance in a sample size of approximately 80 subjects are likely to have limited clinical relevance.

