### Statistical methods

After the last participant has completed all assessments, additional monitoring and data quality checks will be completed. Analyses will be performed by the investigators supported by a biostatistician when needed. All statistical tests will be conducted as two-sided, with the alpha level set at 0.05. Baseline variables and descriptive statistics with continuous data will be presented with mean ± standard deviation (SD) or median with interquartile range (IQR) as appropriate. Ordinal variables will be presented as median (IQR), and categorical variables will be presented as n (%).

Continuous data with normative values (for example lung function values) will be presented both as absolute values and as % of predicted normal values.

The primary outcome is the change from baseline to post intervention, and analyses will be performed with paired statistical testing. Analyses of both absolute change (delta values) and % change will be performed. Age, sex, pack-years and site are potential confounding factors which might be taken into account as co-variates.

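### Sex and age cannot confound a paired within-person change, so the secondary outcome should ask whether the change differs by sex and age

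*Protocol article*

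**What the plan says.** Trial design describes a "multi-center exploratory, hypothesis-generating single group trial", so every participant trains and there is no comparator.

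Statistical methods defines the effect within the person: "The primary outcome is the change from baseline to post intervention, and analyses will be performed with paired statistical testing". Both absolute and percentage change are to be analysed. The same paragraph ends: "Age, sex, pack-years and site are potential confounding factors which might be taken into account as co-variates".

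Other secondary outcomes gives, as its last item: "Validate if gender and age are confounding factors for the effect of the exercise intervention". It names gender and age only. Pack-years and site appear only in Statistical methods, where using them is optional.

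The article names no analysis of whether the change differs by age or sex. Secondary outcomes plans to separate responders from non-responders, but by lung measures and physical capacity. Specific aims and Secondary outcomes also plan correlations of biomarker changes with lung function and physical capacity, and Specific aims adds quality of life.

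**The concern.** A confounder must be associated with the contrast being estimated. Here the contrast is after versus before in the same person. Sex is constant over that interval, and baseline age is a single value per person. Even age at each visit moves by only about 12 weeks, or somewhat more where training is extended after illness or absence. Site is fixed. Pack-years are in effect fixed too, because participants must have stopped smoking at least a year earlier. None of these can explain why the mean differs between the two visits. They can only be related to how much each person changes.

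The question as worded therefore has its answer built in, while the informative one is not asked. That matters because Background and Discussion give individualised therapy as a goal. If the outcome is answered in its own terms, a real difference in change between men and women, or across age, could sit under the finding that sex and age are not confounders.

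**Working it through.** **1. Adjustment cannot move the mean change.** Let D be each participant's change and X the covariates (age, sex and, if used, pack-years, site and baseline value). Fit D = a + b(X − X̄) by least squares. The fitted line passes through the means, so D̄ = a + b(X̄ − X̄) = a. The adjusted mean change a equals the crude mean change D̄ whatever b is. This is algebra and needs no assumption about the data beyond complete pairs. It holds equally for absolute and percentage change.

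**2. Numerical confirmation.** The assumed inputs were 68 pairs, a true mean change of 0.3 SD, age 68 with SD 8, and equal splits by sex and site.
- Over 2,000 simulated trials, the largest gap between crude and centred-adjusted mean change was about 3 × 10⁻¹⁵. That is rounding error, and it held even with strong modification by age and sex.
- In one simulated data set with one row per visit, the time coefficient was 0.3214 both without and with age and sex in the model.
- In that data set the true sex difference in change was 0.60. A sex-by-time term estimated it at 0.68. Main-effect adjustment gave no sign of it.

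**3. Where confounding is possible.** When two change scores are correlated across participants, a shared dependence on age and sex can create the association. In a simulation with no direct link between the two changes, the mean crude correlation was 0.20 and the mean partial correlation given age and sex was 0.00. The word is therefore right for the correlation analyses.

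**4. Precision of the question that can be answered.** Sample size gives 80 participants with 10–20% dropout, and "Of these, 20 will also undergo bronchoscopy". It states no effect size, SD or power, so there is no planned figure to reproduce. If the 80 includes dropouts, complete pairs number 80 × 0.80 = 64 to 80 × 0.90 = 72. Alpha is 0.05 two-sided, as in Statistical methods. Power of 80% is assumed, so the multiplier is 1.960 + 0.842 = 2.802.

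Detectable sex difference, in SD of change, with an equal split = 2.802 × 2/√n. Detectable correlation of change with age = tanh(2.802/√(n − 3)).

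| Pairs | Sex difference, equal split | Sex difference, 35:65 split | Power for 0.5 SD, equal split | Age correlation |
|---|---|---|---|---|
| 72 | 0.66 | 0.69 | 56% | 0.33 |
| 64 | 0.70 | 0.73 | 52% | 0.34 |
| 20 (bronchoscopy) | 1.25 | 1.31 | 20% | 0.59 |

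The last row assumes that all 20 give paired samples. With 16 pairs the equal-split figure rises to 1.40 SD.

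**The case against.** The strongest reply is that this is mostly a matter of labels. Statistical methods already allows age and sex as covariates in an analysis of change, and the coefficients from that model are the effect-modification estimates. The item is the last of the other secondary outcomes in a hypothesis-generating study. Much of this stands. A reader might infer that the planned analysis cannot show a sex or age difference at all, and the documents do not support that. What remains is that the outcome names a different target, and that target has a fixed answer.

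A reader might also infer that adjustment will yield a spurious training effect, because an intercept from uncentred covariates refers to age 0 and 0 pack-years. The article does not say that covariates would be left uncentred, that an intercept would be reported, or that confounding would be judged by the shift in an estimate. Those details are commonly left to an analysis plan, so this part falls.

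A third tempting step is to strike confounding from Statistical methods altogether. That section serves the whole study, including the between-person correlations, where these four variables can confound. Deleting the word would remove a valid safeguard.

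Finally, an analysis of effect modification should not be oversold. Without a control group, a sex or age difference in change may reflect natural course, regression to the mean or test learning.

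**Conclusion.** The point holds as a minor correction to one secondary outcome. In a single-group trial analysed by paired change, sex and baseline age cannot confound the mean change in complete pairs. The outcome as worded can then only return a negative, and the useful question is left unnamed. This rests on the article's own design and analysis statements and on an algebraic identity, not on the simulation settings.

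The primary paired estimates are not affected. The point does not extend to the correlation analyses. It also does not rule out centred covariates for precision.

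The restated question can be answered only coarsely: sex differences of about 0.66 to 0.70 SD of change in blood, urine and functional measures, and about 1.25 SD in the bronchoscopy subset. These figures assume 80% power, an equal sex split, that the 80 includes dropouts, and that all 20 bronchoscopy participants have paired samples.

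**What to change.** - In Other secondary outcomes, replace the item with: whether the change from baseline differs by sex and age.
- Regress change on mean-centred age and sex. Centred baseline value, pack-years and site may be added for precision. Report the age and sex coefficients with 95% confidence intervals, labelled exploratory.
- Describe the results as differences in change, not as proof of who benefits from exercise.
- In Statistical methods, keep confounding for the between-person correlations planned in Specific aims and Secondary outcomes. For the paired change, call the same variables covariates or effect modifiers.
- State the limited precision beside the outcome, with the bronchoscopy subset given separately.

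The cost is a change of wording and one regression per outcome on data already being collected. No added participants, visits or samples are needed.
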